### Outcomes

#### Primary and secondary outcomes

There are two primary outcomes, measured at the physician’s level. One is the proportion of COX-2 inhibitors (anatomical therapeutic classification [ATC] M01AH) prescribed within the entire NSAID class (ATC M01A) in defined daily doses 18 months after the intervention. The other is the proportion of omeprazole (ATC A02BC01) within the entire proton pump inhibitors class (ATC A02BC) in defined daily doses 18 months after the intervention.

There are seven secondary outcomes, also measured at the physician’s level: the proportion of COX-2 inhibitors within the NSAID class at one and six months; the proportion of omeprazole within the proton pump inhibitors class at one and six months; and the number of defined daily doses of clopidogrel prescribed per 1,000 registered patients at 1, 6 and 18 months. The proportion of clopidogrel (ATC B01AC04) within the platelet aggregation inhibitors (ATC B01AC) was not selected as an outcome because the most commonly used drug in that class is acetylsalicylic acid (ATC B01AC06). This drug is generally sold over the counter, and no reliable data of its consumption exists.

#### Timing of outcome collection

Unlike a randomized controlled trial for a drug, we do not expect the intervention to be delivered immediately after allocation. This is because there are a limited number of detailers, and their time for visits is also limited (as they themselves are practicing physicians). Plus, family physicians’ availability to receive visits from these detailers is also constrained by their heavy workload. These constraints will prevent us from delivering the intervention to all physicians in a short period (*e.g.*, less than one month). We plan to deliver the full intervention to all physicians in the experimental group over a period of six months. For each guideline, we will seek to visit all the physicians belonging to the same cluster in the shortest time possible, to limit contamination within clusters. This will cause the gap between allocation and intervention dates to vary depending on the participating unit. Thus, if we assess the outcome at a fixed time following randomization, participating units will have different follow-up times after the intervention, and as a result the observed intervention effect will be unreliable. Moreover, since we will have three visits for each physician, there will also be differences in the time of intervention between guidelines. For these reasons, outcomes will be measured from specific intervention dates rather than from the general allocation date. This will provide more reliable data about the efficacy of the intervention.

Using the intervention dates poses a problem for the control group, for whom these do not exist. If we were to measure outcomes from the allocation date, there would be up to a six-month time gap compared with intervention units. In this relatively long interval, other factors influencing prescription of the study drugs could arise (*e.g.*, new research or guidelines being published, changes in drug policy in the Portuguese NHS, seasonal trends of prescription of NSAIDs, etc.). We will address this problem by randomizing the dates from which we measure outcomes for each guideline among control units. This will distribute control units along the intervention period, making them more comparable to the experimental group. This will be done by selecting a random month falling within the first and last months of the visits in the intervention group. The trial statistician will blindly assign a random month for each guideline in every control unit after the final visit in the intervention group is made and before outcomes are collected.

Outcomes will be measured using the same monthly prescription data for all physicians within a given cluster.

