### Allocation to intervention and blinding

Clusters will be enrolled and allocated randomly. To achieve a good balance regarding baseline characteristics that can influence the outcome, the allocation sequence will be determined by minimization [22]. This stratified randomization method will balance the control and intervention groups for number of physicians (4 or 5, 6 or 7, 8 to 12), median baseline prescription of COX-2 inhibitors (above or below the regional median), median baseline prescription of omeprazole (above or below the regional median), proportion of physicians with fewer than 10 years of practice after completing vocational training (above or below 50%), and type of primary care unit (family health unit or personalized care unit). All physicians sending the consent statement before the cluster allocation will be included in the study.

The sequence of intervention visits for each unit will be determined by simple randomization.

Allocation concealment will be ensured by the following procedures: the trial manager (hired and not part of the authors research team) will assign a sequential number to each unit as participation forms are received; only anonymized data about participating units will be sent to the trial statistician (sequential number and minimization variables); data will be sent in two batches, one for each half of all units; the sequence of visits will be determined using the random sequence generator from Random.org (http://www.random.org/sequences/); the statistician will blindly allocate units to each trial arm using minimization and return allocation information to the trial manager.

Due to the nature of the intervention, neither family physicians nor detailers can be blinded. Outcomes are routinely collected by the regional health administration independently of the researchers or the trial and will only be sent to researchers after the intervention has ended. Upon receiving prescription data, the trial manager will generate a random code (using http://www.randomcodegenerator.com) to designate intervention and control units and another code for the order of the visits. Data analysts (the trial statistician plus one of the members of the research team) will receive a file with these codes, ensuring they will be blinded to group and visit sequence allocation until all analyses are completed.

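### Control index months are drawn between the first and last visit months and ignore how visits were spread, so uneven or late visits leave a calendar gap between the arms

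*Protocol article*

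**What the plan says.** The protocol article, Timing of outcome collection, sets the clock differently in the two arms.

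- Intervention units: "outcomes will be measured from specific intervention dates rather than from the general allocation date".
- Control units have no visit date, so one is drawn: "This will be done by selecting a random month falling within the first and last months of the visits in the intervention group".
- The draw comes once all visits are done but ahead of any outcome data: "The trial statistician will blindly assign a random month for each guideline in every control unit after the final visit in the intervention group is" (sentence cut here).
- One calendar month per guideline applies to a whole unit: "Outcomes will be measured using the same monthly prescription data for all physicians within a given cluster".

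The reason given is calendar-time comparability. The section names new research or guidelines, "changes in drug policy in the Portuguese NHS, seasonal trends of prescription of NSAIDs, etc" as influences that could separate the arms, and says of the random month: "This will distribute control units along the intervention period, making them more comparable to the experimental group".

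On the visit calendar itself, the section says: "We plan to deliver the full intervention to all physicians in the experimental group over a period of six months". It also expects the time from allocation to visit to vary by unit, because detailers and physicians have limited time. Intervention and comparison allows a visit to be rescheduled up to the day before and gives no latest date for the new appointment.

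**The concern.** The draw uses two facts about the visits, the earliest and the latest month. It does not use how many units were visited in each month, although that is known by then. Real visits follow the availability of detailers and physicians, so there is no reason to expect them to be even.

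Outcomes are read at 1, 6 and 18 months from the index month, so a difference in index months carries over unchanged to every outcome, including both primary ones. Any drift in the share of COX-2 inhibitors or omeprazole over that gap enters the treatment contrast and cannot be told apart from an effect of the visits.

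**Working it through.** **Inputs from the protocol article.** 38 units allocated 1:1, so 19 per arm; target difference 5 points; COX-2 share SD 7.4 points, ICC 0.249, six physicians per unit, alpha 0.025, power 80%, dropout 15% (Sample size); planned visit window six months (Timing of outcome collection).

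**Assumptions.** The article gives no visit calendar and no trend. The calendars below, the trend of 0.1 to 0.5 points per month, and equal probability for each month in the range are assumptions.

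**The plan's own figure.** The plan gives no number for the calendar gap. Its sample size reproduces. For COX-2 the unadjusted n is 41.64 per group (two-sided alpha 0.025), the design effect is 1 + 5 × 0.249 = 2.245, and 41.64 × 2.245 / 0.85 = 110. The standard error of the COX-2 contrast that this implies, with 110 × 0.85 = 93.5 physicians per arm, is √(2 × 7.4² × 2.245 / 93.5) = 1.62 points.

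**Formulas.** If visits run from month 1 to month L, the expected control index month is (1 + L)/2. If one of 19 units moves from month 6 to month 6 + k:

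- the expected control mean rises by k/2;
- the intervention mean rises by k/19.

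For k = 3 these are 1.5 months and 0.16 month.

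**Gap (control minus intervention), in months.** Front-loaded means 6, 5, 3, 2, 2, 1 units in months 1 to 6, with mean 49/19 = 2.58. Back-loaded is the reverse, with mean 84/19 = 4.42.

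| Assumed calendar | Intervention mean | Expected control mean | Gap |
|---|---|---|---|
| Even or symmetric, none late | 3.50 | 3.50 | 0 |
| Front-loaded, none late | 2.58 | 3.50 | +0.92 |
| Back-loaded, none late | 4.42 | 3.50 | −0.92 |
| Even, one unit 3 months late | 3.66 | 5.00 | +1.34 |
| Front-loaded, one unit 3 months late | 2.74 | 5.00 | +2.26 |
| Back-loaded, one unit 3 months late | 4.58 | 5.00 | +0.42 |

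With one unit three months late, an expected 19 × 3/9 = 6.3 control units are indexed in months 7 to 9, where only one intervention unit lies.

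**Bias from a linear trend = gap × trend.**

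- Gap 1.34: 1.34 × 0.1 = 0.13 to 1.34 × 0.5 = 0.67 points.
- Gap 2.26: 2.26 × 0.1 = 0.23 to 2.26 × 0.5 = 1.13 points.

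The full range of 0.13 to 1.13 points is 3% to 23% of the 5-point target, or 0.08 to 0.70 of the COX-2 standard error. The sign depends on the direction of the trend and on whether controls are indexed later or earlier.

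**Equal means are not equal calendars.** For a symmetric hump (1, 3, 5.5, 5.5, 3, 1 of 19 units) the mean gap is zero, but about 25% of the two month distributions still does not overlap. A linear trend then causes no bias; a seasonal pattern could.

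**The case against.** The rule is a sensible one. Its stated alternative, indexing controls at allocation, could leave a gap of up to six months, and the article claims only to make the arms more comparable. The draw is blind and precedes outcome collection. With even visits and no straggler the expected gap is zero, and with back-loaded visits a straggler can shrink it. A visit missed without warning is not rescheduled, which limits some late visits. Both primary outcomes are shares within a drug class, so a seasonal rise in NSAID volume does no harm unless the COX-2 mix changes too. The article does not say that the draw is uniform, nor whether the range is specific to each guideline. All of this stands, and it makes the problem conditional and its likely size modest. It does not answer why the draw should ignore a calendar that is already known.

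A reader might infer more than the document supports:

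- *That one late visit shifts the whole control arm.* It widens the range. The expected control mean moves by half the delay, and a visit that is late but still inside the range changes nothing.
- *That a gap of about two months is to be expected.* That takes front-loading and an overrun of the six-month window together, and the article gives no sign that both will occur.
- *That chance imbalance in the draw costs precision.* Even if both arms' months were random over six months, the standard error of the difference in mean month would be √(35/12) × √(2/19) = 0.55. At 0.5 points per month that is 0.28 points, and √(1.62² + 0.28²) = 1.64, an increase of about 1.5%.
- *That a control unit could be indexed before its own allocation.* The article says "data will be sent in two batches, one for each half of all units", but nowhere that visits begin before the second batch is allocated. The 18-month outcome would in any case fall well after allocation.
- *That a missing calendar-month term in the model is an error.* That is ordinary content for an analysis plan, which is not shown.

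**Conclusion.** The point holds as a moderate and conditional weakness in a stated rule. The control index months follow the extremes of the visit calendar and not its shape, so the rule reaches its aim only if visits happen to be even or symmetric with none late. The size rests on the assumed calendars and trend and on the uniform reading of the draw. Under those, bias lies between nothing and about 1.1 points, at worst under a quarter of the target difference. The sample size is not affected.

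**What to change.** Replace the sentence on the random month. After the last visit, list the set of three guideline months for each intervention unit, without unit identities. The statistician then blindly gives each control unit one set chosen at random without replacement, reusing sets where the control arm has more units.

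With equal arms the two calendars are identical for any visit pattern, and the order and spacing of the three guidelines are preserved. A late unit then moves both arms alike, by 3/19 = 0.16 month for a three-month delay. If the arms differ in number, some sets are reused or left out and the calendars match only approximately, but the expected gap is still zero.

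The cost is one changed sentence and a different draw at the time already planned. It needs no extra units, physicians or data, and the Trial status section reports that no unit had been randomized at submission.

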### Cost analysis

Global prescription spending will be defined as the sum of the cost of all drug prescriptions of NSAIDs (ATC M01A), acid suppressive therapy (proton pump inhibitors ATC A02BC and their alternatives: H_2_-receptor antagonists ATC A02BA, antacids ATC A02A, misoprostol ATC A02BB01, and sucralfate ATC A02BX02), and antiplatelets (ATC B01AC), up to 18 months after the intervention. These costs will be compared with the amount spent training the detailers, preparing and printing educational materials, travel expenses to intervention units, payment of detailers, program coordination, and physician time spent with a detailer rather than with a patient. Costs will be analyzed from the point of view of an educational outreach program rather than from conducting research. Therefore, research related costs (such as researcher time for data collection and analysis) will not be considered. Similarly, the unrelated training session offered to the control units will not be accounted for because it is only intended to improve recruitment and would not be necessary for the implementation of an educational outreach program.

### Data collection

Researchers will have access to prescription data through a data monitoring system operated by the Regional Health Administration. Data will be collected and provided by employees from this Administration according to researcher defined specifications. Importantly, researchers will not be directly involved in data collection. This information arrives with a two-month delay from the date the prescription is dispensed. The prescription information contained there can be either for acute conditions - single prescriptions with up to two packages to be dispensed within 30 days; or for chronic usage - three identical prescriptions (up to two packages each) to be dispensed within 6 months. Within the drug classes of this study, only NSAIDs cannot be prescribed for chronic usage. Adverse events cannot be collected in this study because only prescription data is available.

Detailers will record whether the planned visit was effectively accomplished, whether it had the planned duration, the number of physicians (including residents) present, whether the visit was made on patient visit time or off hours, the number of times the detailer had previously visited that physician, and feedback from the physician about the educational materials.

### Sample size

The research team has obtained pilot data from all physicians of three primary care units. This data was used to estimate within unit variability and the intra-cluster correlation coefficient (ICC). Data was also gathered for all the units in the Regional Health Administration to estimate the mean prescription and standard deviation for the primary outcomes. The mean proportion of omeprazole dispensed was 54.0% of all PPIs (standard deviation, SD, 10.1%) and the ICC was 0.027. The mean proportion of COX-2 inhibitors dispensed was 20.6% of all oral NSAIDs (SD 7.4%), and the ICC was 0.249. The Cochrane review on educational outreach visits found a median adjusted risk difference for improvement in compliance with desired practice of 5.6% (interquartile range 3.0% to 9.0%) and 4.8% specifically for prescribing (interquartile range 3.0% to 6.5%) in previous trials [10]. Therefore, we chose to calculate our sample size assuming the intervention would lead to a 5% absolute difference in compliance with guidelines between intervention and control units.

If we assume a mean cluster size of six physicians per unit, a 1:1 allocation ratio of controls per intervention unit, an alpha type error of 0.025, and a dropout rate of about 15%, then a sample of 110 physicians in each group will allow for 80% power to demonstrate a 5% absolute increase in the proportion omeprazole and a 5% absolute decrease in COX-2 inhibitors. To recruit the necessary number of physicians, 38 primary care units will be required. STATA 12.0 (STATA Corp, TX, USA) and its sampsi and sampclus commands were used to calculate sample size.

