### Statistical methods

Physicians will be analyzed according to their randomly allocated group regardless of adherence to the intervention (intention to treat analysis). If physicians transfer to another unit within the health region, we will still be able to monitor their prescriptions. If the transfer is to a different health region (*i.e.*, not Lisbon) we will contact the physician and ask for the missing prescription data. In both cases, prescription of clopidogrel will be adjusted to the new patient list. If a physician retires or we are unable to retrieve data from a physician who moved to a different region, then we will use the last working month’s prescription.

Both groups will be compared on primary outcomes using generalized mixed-effects models. The ratio of COX-2 inhibitors to the entire NSAID class and the ratio of omeprazole to the entire proton pump inhibitor class and respective 95% confidence intervals will be calculated. Statistical significance will be assumed for a p-value less than 0.025. STATA 12.0 (STATA Corp, TX, USA) will be used to conduct the analysis.

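### Testing both primary outcomes at a fixed p<0.025 is valid but less powerful than Holm's step-down at the same familywise error, and the 80% power should be labelled as applying to each outcome separately

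*Protocol article*

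**What the plan says.** The outcomes section of the Protocol article states "There are two primary outcomes": the COX-2 share of NSAIDs and the omeprazole share of proton pump inhibitors, both at 18 months. The Sample size section uses "an alpha type error of 0.025" and a 5-point effect on each outcome, and concludes that 110 physicians per group "will allow for 80% power to demonstrate a 5% absolute increase in the proportion omeprazole and a 5% absolute decrease in COX-2 inhibitors". The Statistical methods section fixes the decision rule: "Statistical significance will be assumed for a p-value less than 0.025". It gives no step-down rule, and it plans 95% confidence intervals. The article does not say whether the tests are one- or two-sided, and it gives no correlation between the two outcomes.

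**The concern.** Two things stand out.

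First, a fixed 0.025 for both outcomes is plain Bonferroni. If one outcome is clearly positive and the other has p=0.03, the second must be called non-significant. Holm's procedure would declare it significant while still holding the familywise error at 0.05. The two outcomes carry two different guideline messages, so losing one of them would matter for deciding what an outreach programme can deliver.

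Second, the power sentence attaches one figure to two effects joined by a conjunction, with no word such as "each" or "separately". A reader could take 80% as the chance of showing both effects.

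**Working it through.** **Inputs (Sample size section).** Difference 5 points; SD 10.1 and ICC 0.027 for omeprazole; SD 7.4 and ICC 0.249 for COX-2; mean cluster size 6; 1:1 allocation; dropout 15%; alpha 0.025; power 80%.

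**Step 1: reproduce the stated sample size.** Per arm, n0 = 2 × SD² × (2.241 + 0.842)² / 5², multiplied by the design effect 1 + (6 − 1) × ICC and divided by 0.85.

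- COX-2: n0 = 41.64; design effect 1 + 5 × 0.249 = 2.245; 41.64 × 2.245 / 0.85 = 110.0.
- Omeprazole: n0 = 77.57; design effect 1 + 5 × 0.027 = 1.135; 77.57 × 1.135 / 0.85 = 103.6.

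The stated 110 is therefore the larger of two separate calculations. Two-sided 0.025 is inferred: one-sided 0.025 or two-sided 0.05 gives at most about 93 and does not match.

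**Step 2: power for each outcome at 110 per arm.** Evaluable physicians per arm: 110 × 0.85 = 93.5. The expected z-statistic is 5 / (SD × √(2 × design effect / 93.5)), which is 3.177 for omeprazole and 3.083 for COX-2.

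| Outcome | Power at 0.025 (critical value 2.241) | Power at 0.05 (critical value 1.960) |
|---|---|---|
| Omeprazole | 82.5% | 88.8% |
| COX-2 | 80.0% | 86.9% |

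**Step 3: fixed 0.025 against Holm, independent test statistics.**

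- Both, fixed rule: 0.8253 × 0.8001 = 0.660.
- Both, Holm: 0.8253 × 0.8694 + 0.8882 × 0.8001 − 0.8253 × 0.8001 = 0.768.
- COX-2, Holm: 0.8001 + (0.8694 − 0.8001) × 0.8253 = 0.857.
- Omeprazole, Holm: 0.8253 + (0.8882 − 0.8253) × 0.8001 = 0.876.

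**Step 4: other correlations.** Joint power under the fixed rule comes from the bivariate normal distribution. The Holm columns come from 2,000,000 simulated draws, which agree with step 3 to within about 0.1 point. The correlation is an assumption.

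| Correlation | Both, fixed 0.025 | Both, Holm | COX-2, Holm | Omeprazole, Holm |
|---|---|---|---|---|
| 0 | 66.0% | 76.9% | 85.8% | 87.6% |
| 0.3 | 68.5% | 78.2% | 85.3% | 87.0% |
| 0.5 | 70.4% | 79.3% | 84.9% | 86.6% |
| 0.9 | 76.4% | 82.7% | 83.9% | 85.1% |

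The chance of at least one significant outcome is the same under both rules (96.5% at correlation 0), because Holm's first step is the Bonferroni test.

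**Step 5: error rates.** If neither outcome is affected, both rules have the same familywise error: 1 − 0.975² = 0.049 when independent, and lower with positive correlation. If one outcome is truly affected and the other is not, the fixed rule makes a false claim on the unaffected one with probability 0.025. Under Holm, assuming independence, this becomes 0.025 + 0.025 × 0.825 = 0.046 for COX-2 when omeprazole is affected, and 0.025 + 0.025 × 0.800 = 0.045 the other way round. It cannot exceed 0.05, since Holm never rejects at a p-value above 0.05.

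**The case against.** The plan is internally consistent: two primary outcomes, sized at 0.025, tested at 0.025. Bonferroni is a valid choice, and the sample size reproduces. All of this stands, so nothing here is a validity error.

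A reader might infer from the power sentence that the protocol claims 80% power to show both effects, and so that it overstates its power or is too small. The document does not support that. Halving alpha makes sense when either outcome alone can carry a claim; if both had to succeed, no split would be needed. The Stata commands the section names size one outcome at a time, and nowhere does the article require both outcomes to succeed. The sentence is ambiguous, not false.

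A reader might also infer that Holm is free. It is not. It costs nothing in familywise error or sample size, but step 5 shows that it nearly doubles the false-claim rate on an unaffected outcome when the other is truly affected. A fixed 0.025 rule also has simple matching 97.5% intervals, and Holm has none as simple. A team could reasonably prefer the stricter rule for each outcome. Against this, the planned intervals are 95% and so do not match the 0.025 threshold as the text stands.

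Finally, the joint figures depend on a correlation that the document does not give, and the ICCs come from three pilot units. Both limit how precisely the gain can be stated.

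**Conclusion.** The point holds as an inexpensive improvement together with a clarification of wording. Holm rejects everything that the fixed rule rejects, and sometimes more, at the same familywise 0.05 and the same sample size. The gain is about 5 to 6 points for COX-2, 4 to 5 points for omeprazole, and 9 to 11 points for both, at correlations of 0 to 0.5. A higher correlation narrows the joint gain: at 0.9 it is about 6 points. These figures rest on two-sided testing (inferred), a normal approximation, equal clusters of six, 15% dropout and no baseline adjustment. With 19 × 6 = 114 per arm, joint power is 68.5% to 72.5% under the fixed rule and 79% to 81% under Holm for the same correlations.

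The 80% figure is correct for each outcome taken separately. It should not be read as the power to show both, nor as evidence that the sample size is wrong.

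**What to change.** 1. In Statistical methods, replace the fixed threshold with Holm's procedure: test the smaller of the two primary p-values at 0.025 and, if it is significant, test the other at 0.05. State that the tests are two-sided, if that is what was intended.
2. In the same place, add a note on which confidence level accompanies each step of the procedure.
3. In Sample size, say that 110 physicians per group give 80% power for each primary outcome separately at 0.025. If joint power is quoted, give the assumed correlation with it: about 66-70% under the current rule, or 77-79% under Holm, for correlations of 0 to 0.5.

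The cost is a few sentences and no extra physicians. The team accepts a false-claim rate of up to 0.05, instead of 0.025, on one outcome when the other is truly affected, and intervals that are less simple to match to the decisions. The Trial status section reports that no unit had been randomized when the article was submitted, so at that stage the rule could be changed without loss of prespecification.
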